## Abstract

**Background:**

Chronic Kidney Disease (CKD) is a pressing global health concern that is placing increased strain on health care resources. CKD patients regularly receive peritoneal dialysis as a common CKD treatment. An emerging technological solution is telehomecare as way to support patients receiving PD in their homes. This study protocol outlines a mixed methods evaluation exploring a telehomecare developed to enhance CKD patients’ outcomes and experiences. The study aims to assess the usability, acceptability and scalability of this virtual care application.

**Methods:**

A realist evaluation using an embedded case study design will be used to understand the usability, acceptability and scalability of a telehomecare application for patients with CKD undergoing PD. The realist evaluation that is further described in this paper is part of a larger evaluation of the eQ Connect™ intervention that includes a randomized, parallel-arm control trial aimed at determining if utilizing eQ Connect improves selected clinical outcomes for PD patients (CONNECT Trial).

**Discussion:**

Potential implications of this study include elucidating which components of the intervention are most effective and under what conditions with a focus on the contextual influences. Collectively, our multi-method design will yield knowledge around how best to implement, sustain and spread the telehomecare application that will be useful to guide the development, implementation and evaluation of future virtual care applications aimed at improving the quality of care outcomes and experiences of patients.

**Trial registration:**

NCT02670512. Registered: January 18, 2016.

## Background

Over 70 million individuals worldwide have Chronic Kidney Disease (CKD) making it a pressing global health concern that is placing increased strain on health care resources related to CKD care [1, 2]. The prevalence of CKD stages 1 to 4 has increased dramatically from 10% in 1988–1994 to 13% in 1999–2004 in the United States [3] and 12.5% (representing 3 million adults) from 2007 to 2009 in Canada [4]. These higher rates of chronic disease may also lead to adverse outcomes and end stage renal disease (ESRD) requiring dialysis or kidney transplantation [5]. Globally, approximately 190,000 patients regularly received peritoneal dialysis (PD) [6] which is usually performed at home daily by the patient after receiving education and training by a dialysis health care professional [7, 8]. PD has been associated with a survival advantage, especially in the first few years of therapy [9–11]; is the least costly of all the forms of dialysis (e.g. in Canada it has been recently estimated that maintaining a patient on PD compared to hemodialysis saves the healthcare system over $150,000 over a three year period [12]; and higher levels of satisfaction with care than patients receiving hemodialysis [7]; and higher health-related quality of life (HrQOL) scores [13, 14].

Regardless of treatment for CKD, care is complex and requires significant personal involvement to integrate medication adherence, lifestyle modification and nutritional adaptation into a daily routine [15]. CKD patients are often not satisfied with their communication with their health care providers and are frequently unaware of their diagnosis or its implications [16–18]. This may be due in part to the volume of CKD patients which have resulted in nephrologists seeing more patients in less time [19]. Simultaneously, alternative methods of communication are being developed and embraced by a population with growing computer literacy [20]. Emerging new technological solutions including the variety of applications and portals for health information are offering patients a better understanding of their diseases and evidence informed practice [19].

One emerging technological solution is telehomecare, which refers to a model of care using information, communications, measurement and monitoring technologies to enable healthcare providers to link with patients at home [9, 21]. Telehomecare has been associated with reduced risk of disease and other health-related problems and improved recovery in other patient populations [22, 23]. Specific examples include less symptoms and fewer hospitalizations for persons with heart failure [22], increased compliance rates and feedback in cardiac rehabilitation patients [23], and improved quality of life indicators in the pediatric palliative care population [24]. Further, telehomecare can reduce costs associated with improved coordination, continuity of care, and access to specialized care [20, 25, 26].

Although promising signs are emerging with various technologically enabled virtual care solutions for a variety of chronic illnesses, few are being employed with CKD [19]. Given that PD is performed in a home setting, patients using this modality are ideal candidates for support and monitoring using telehomecare services. Successful implementation of telehomecare is a complex, multi-factorial endeavor [27]. Although there is growing support for more process evaluation [28], much less attention is being paid to the mechanisms for delivering interventions [29] and the future scalability of interventions [27, 28, 30]. In this context, this paper provides the protocol for a realist evaluation that aims to understand how a telehomecare application aimed at enhancing CKD patients’ outcomes and experiences is implemented in practice, and to assess the usability, acceptability and scalability of this virtual care application. Realist evaluations are used to identify which components of the intervention are most effective and under what conditions with a focus on the contextual influences [29, 31, 32].

## Methods

### Study design

A realist evaluation [29, 31, 32] using an embedded case study design [33] will be used to understand the usability, acceptability and scalability of a telehomecare application for patients with CKD undergoing PD. Through this type of design, researchers are able to understand how and why the implementation succeeds or fails. A realist evaluation 1) provides an explanation for why study outcomes occur; 2) involves multi-methods involving quantitative and qualitative approaches; and 3) uses a theory-driven approach that guides the study design [32].

This realist evaluation will be guided by the RE-AIM Conceptual Framework [34] and the Institute of Healthcare Improvement (IHI)’s Triple Aim [35] and Framework for Going to Full Scale [36]. These were selected by the research team to provide an evidence-informed, comprehensive, and contemporary framework to guide the study. Key concepts of the RE-AIM framework that underpin scalability include reach, effectiveness, and adoption (see Table 1). IHI’s Triple Aim focuses on the extent to which health care innovations result in 1) improved population health, 2) enhanced patient experience, and 3) reduced health care costs, synergistic with the RE-AIM model’s effectiveness domain [35]. The phases of the IHI framework include 1) set-up, 2) develop the scalable unit, 3) test of scale-up, and 4) go to full scale [36]. Key elements include adoption mechanisms (i.e., leadership engagement, communication methods, leveraging social networks, and building a culture of urgency and persistence); support systems needed to achieve large-scale programming (i.e., a learning system that connects adopters and experts, a data system to support measurement for improvement, infrastructure such as IT, equipment, etc.), building capability through training and support, and building reliable processes that support sustainability [36].

**Table 1 Tab1:** RE-AIM Framework

RE-AIM Framework Dimension	Description
Reach	Our scalability assessment will pay close attention to the “reach” of the telehomecare initiatives, which has important implications for their potential implementation across the province.
Effectiveness	We will explore perceptions and experiences associated with their participation in the demonstration initiative guided by the Institute for Healthcare Improvement’s (IHI) Triple Aim of 1) improving population health, 2) enhancing patient experience, and 3) reducing health system costs.
Adoption	Our process evaluation will explore the extent to which health care practitioners and other key stakeholders agree to deliver the intervention as intended.
Implementation	Our process evaluation will focus explicitly on how and why the telehomecare initiatives are implemented in particular ways across different contexts.
Maintenance	Our scalability assessment includes the assessment of whether key stakeholders would continue delivering the telehomecare initiatives outside the scope of the research study over time.

For this study, we hypothesize that successful adoption and scalability of the intervention will be influenced by a series of mechanisms including leadership engagement and culture, communication methods, social network, and reliable processes; structures including a learning system that includes training and support and infrastructure that connects adopters and experts, a data system to support measurement for improvement; that result in positive patient related outcomes and experiences.

### Intervention description

The CONNECT Trial Research Program was established to further investigate a telehomecare monitoring software (eQ Connect™ system, developed by eQOL Inc.) intended for use by patients on PD. The software provides support for patients undergoing PD through enabling communication between patients and the healthcare team, providing up-to-date patient health information, and ensuring patient compliance with PD regimens, and is intended to ultimately reduce barriers for PD uptake. The patient-facing part of eQ Connect™ (Patient Portal) is built to run on a mobile tablet, allowing for mobility, uncomplicated data recording, and ease of uploading data securely over the Internet. Information such as treatment progress, health status, supply usage, etc. is transferred to a secure data center when an Internet connection is available and the information is accessible to the patient’s health care team from this center. The clinician-facing part of eQ Connect™ (Support Portal) is built on web technologies. See Fig. 1. Clinicians are able to gain access to the information entered by the patient through the application after securely logging in from any Internet web browser. This reduces the need to install additional software thereby utilizing existing computer infrastructure within hospitals and clinics.

**Fig. 1 Fig1:**
[figure not shown]
eQConnect Support Portal

The realist evaluation that is further described in this paper is part of a larger evaluation of the eQ Connect™ intervention that includes a randomized, parallel-arm control trial (RCT) aimed at determining if utilizing eQ Connect improves selected clinical outcomes for PD patients (CONNECT Trial). The trial expects to enroll 500 APD/CAPD patients (250 intervention, 250 control) from across Canada.

One-year data was obtained from PD patients at London Health Sciences Centre to generate the baseline estimates of rates of technique failure, infections and hospitalizations. To determine the average rate of the outcome, we calculated the proportion of patients having at least one event, and cumulative incidence of the first and all events. The rate per 1-person time year can be calculated as a crude total, a crude average or from the regression model for count data. This resulted in rates ranging from 0.8766 to 3.4. Four different sample sizes equations were used to calculate the desired sample size based on our proposed analytic plan, which includes: proportions (generally considered conservative), based on the Cox PH/Poisson regression, inflating the Cox regression for correlation within patients and based on Lachin's formula (allowing for time and incompletely follow up). All sample size equations were calculated using a 5% two-sided level of significance, 80% power and assuming a 1 year follow up. Based on the baseline estimates, we allowed parameter values to vary as follows: baseline rate per patient-year from 0.8 to 3.4 and relative risk reduction of 0.2 to 0.35 (by 0.05). Given the funding sources and availability of patients, we can realistically enroll approximately 500 patients. Using the Lachin formula, we are adequately powered to detect a 0.25 or higher relative risk reduction for baseline rates of 2.0 or higher. This is based on a sample size equation that allows for rates with variable follow up time per patient.

Recruitment will occur continuously over a 2 year period to meet the target participant population. The study protocol for this trial has been approved by the Western Research Ethics Board (#107839) through Clinical Trials Ontario and recruitment is in progress.

#### Setting

Participants will be recruited from two hospitals, one urban teaching hospital (London Health Sciences Centre) and one community hospital (Humber River Hospital), both located in Ontario Combined, there are over 200 PD patients receiving care from the two centres. Eligible patients will be approached during their regularly scheduled clinic visit at the PD clinic.

### Objectives

The objectives of the qualitative realist evaluation component of this study is to 1) understand how the eQ Connect™ application is implemented in practice, (2) explore participants’ perspectives of the usability and acceptability of the eQ Connect™application, and 3) examine the key issues associated with scaling applications such as eQ Connect™.

### Quantitative component - outcome measures

Data regarding Patient Reported Outcomes and Experiences (PROMs/PREMs) will be collected by administering a short survey to patients enrolled in the trial by providing an information letter. These standardized PROMs/PREMs will be collected at baseline and 3 months for about 200 participants in both study arms. Patients will be consented into this study at the same time they are consented into the clinical trial study. Baseline data will be collected in-person at the clinic during the RCT baseline data collection. The 3 months data collection which will include the administration of a Mobile App Rating Scale (adapted version) [37] will be synchronized with the 6 month follow-up interview for the RCT. The questionnaires – Patient Reported Costs and Patient Reported Experience - are based on the Better Access and Care for Complex Needs (BeACCoN) Measurement Framework for Evaluation of Primary and Integrated Health Care Innovation for Individuals with Complex Needs. This framework is adapted from the Commonwealth Fund Survey, Patients with Complex Needs and the Canadian Institutes of Health Research Community Based Primary Health Care Survey [38].

### Qualitative component

The qualitative component will include interviews with key stakeholders involved in the implementation process. Specifically, interviews will take place either face-to-face or in a private space at the hospital or through a telephone conversation. Interviews will be conducted between baseline and 3 months. Participants recruited for interviews will include 10 to 12 patients (caregivers will be invited to participate in those interviews as well); 4 to 6 health care providers involved in the implementation process (including at least one physician in each location); 2–4 organizational leaders who oversee the implementation process (for example, Clinic Managers); and 5–7 health system decision makers involved in the implementation of virtual care initiatives in Ontario.

Qualitative interviews will include questions about 1) participants’ experiences of learning about and using the technology; 2) changes to health care provider workflow required to effectively use the technology; 3) organizational changes required to support the technology; and 4) health system barriers and facilitators to effective implementation and evaluation. The interview guide also includes specific questions related to the feasibility of the evaluations taking place, offering participants the opportunity to provide direct input into the implementation and rapid evaluation framework. These qualitative interviews will be analyzed using thematic analysis strategies [39] by the investigative team to identify key themes related to the implementation an evaluation of the virtual care initiatives in actual contexts of health care delivery in Ontario.

### Recruitment

#### Patients/care-givers

Potential participants will be identified prospectively by a research coordinator during the RCT process. Interested patients will then be consented for the quantitative phase as per the materials and processes outlined in the quantitative protocol. Baseline data will also be collected at this time as per the quantitative protocol. During this initial consent process, an Information Letter outlining the PROMs and PREMs and the qualitative phase of the study will be distributed to individuals who consent to participation in the overall trial. The qualitative component is optional and participants who express interest, the research coordinator will obtained the potential study participants name and contact information which will then be provided to the qualitative researcher coordinator. The qualitative research coordinator will then subsequently contact the potential study participant and provide an overview of the study; obtain consent for interested study participants; schedule and conduct the interview.

#### Health care providers/administrators/stakeholders

Qualitative research team will be introduced to the HCPs at the study sites to introduce the qualitative evaluation. The qualitative component for the HCPs consists of an individual interview (either in person or via telephone).

#### Organization leaders

The Organization Leaders (OLs) names will be forwarded to the qualitative team members by the implementation team and the clinical site leads. Potential participants will be notified that they will be contacted via email by the qualitative research team. Further potential OL participants will be identified by asking each participant for further suggestions regarding individuals to contact for potential participation.

#### Health system decision makers

As a first wave of recruitment, the research team will ask the project evaluation contact to identify key individuals involved in the selection and procurement of virtual care technologies, and their subsequent introduction into the health care system. Potential participants will be notified that they will be contacted via email by the qualitative research team and an email invitation will be sent to individuals by the research coordinator.

As a second wave of recruitment, we will use snowball sampling by asking interview participants to identify other health system decision makers who are involved in the processes of around the selection, procurement, implementation, and ongoing support of telehomecare technologies.

### Data analysis

#### Quantitative data

PROMs and PREMs will be analyzed utilizing an intention to treat principle. Patient characteristics will be summarized as means and 95% confidence intervals, medians and interquartile ranges, and frequencies. Differences in patient characteristics across study arms will be compared using independent sample t-tests, Wilcoxon-Mann-Whitney tests, and/or Chi-square tests, as appropriate. The mean difference will be used to compare PROMs and PREMs between the intervention and control arms at 6 months. Within-group outcomes will be analyzed using paired t-tests and Wilcoxon-Mann-Whitney tests. All statistical analyses will be performed using SAS version 9.4 (SAS Institute, Cary, NC).

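### The only between-arm analysis named for the PROMs/PREMs has no baseline term, although baseline scores are collected; adjusting for them is a free gain in precision

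*Protocol article*

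**What the plan says.** The section on quantitative outcome measures sets the collection schedule: "These standardized PROMs/PREMs will be collected at baseline and 3 months for about 200 participants in both study arms". It adds that "Baseline data will be collected in-person at the clinic during the RCT baseline data collection". The same section ties the 3-month collection, which also includes an adapted Mobile App Rating Scale, to a later trial visit: it "will be synchronized with the 6 month follow-up interview for the RCT".

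Under Data analysis, Quantitative data, the comparison of the randomised arms is given in one sentence: "The mean difference will be used to compare PROMs and PREMs between the intervention and control arms at 6 months". The governing principle is that "PROMs and PREMs will be analyzed utilizing an intention to treat principle". The only other outcome analysis is within arms: "Within-group outcomes will be analyzed using paired t-tests and Wilcoxon-Mann-Whitney tests". That section names no baseline covariate, change score, ANCOVA or longitudinal model for comparing the arms.

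**The concern.** A baseline value of the same instrument is often the best available predictor of the follow-up value. Here it is collected, but the only stated analysis that could draw on it is the within-arm paired comparison, which does not estimate the effect of the intervention. The stated comparison of arms does not use it.

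What is at stake is efficiency. The sub-study is smaller than the parent trial, for which "The trial expects to enroll 500 APD/CAPD patients (250 intervention, 250 control) from across Canada", and the article gives it no power statement of its own. The Setting section puts the combined peritoneal dialysis population of the two hospitals at just over 200, so precision can hardly be bought there by recruiting more patients. The baseline score offers it at no cost in data collection.

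**Working it through.** **The plan's own figure.** The article has no power calculation, SD or correlation for the PROMs/PREMs. Its one power statement concerns event rates in the parent trial: at least 80% power with about 500 patients for a relative risk reduction of 0.25 at a rate of 2.0 or more per patient-year. It reproduces. Take φ(λ) = λ²/(1 − e^(−λ)) for one year of follow-up, control rate 2.0, intervention rate 1.5 and mean rate 1.75:

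- φ(2.0) = 4.626, φ(1.5) = 2.896, φ(1.75) = 3.707
- N = [1.960·√(4 × 3.707) + 0.842·√(2 × 4.626 + 2 × 2.896)]² / 0.5² ≈ 468
- power with 500 patients = 82.6%

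This figure is not an input to the present point.

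**Inputs for the sub-study.**
- Size: about 200, read as the total over both arms, so n = 100 per arm.
- Two-sided 5% and 80% power: borrowed from the parent trial's calculation as a yardstick.
- Correlation r between baseline and follow-up score: not in the documents; assumed, with range 0.2 to 0.7.

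**Formulas, in units of the follow-up SD.**
- Unadjusted detectable difference = (1.960 + 0.842) × √(2/n) = 2.802 × √(2/100) = 2.802 × 0.1414 = 0.396.
- Unadjusted 95% CI half-width = 1.960 × 0.1414 = 0.277.
- Baseline-adjusted (ANCOVA): multiply each by √(1 − r²).
- Size of an unadjusted study with the same precision = 200/(1 − r²).

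| Analysis | √(1 − r²) | Detectable difference (SD) | CI half-width (SD) | Reduction in SE | Equivalent total size | Power at 0.396 SD |
|---|---|---|---|---|---|---|
| Unadjusted | 1 | 0.396 | 0.277 | – | 200 | 80% |
| ANCOVA, r = 0.2 | 0.980 | 0.388 | 0.272 | 2.0% | 208 | 82% |
| ANCOVA, r = 0.3 | 0.954 | 0.378 | 0.264 | 4.6% | 220 | 84% |
| ANCOVA, r = 0.5 | 0.866 | 0.343 | 0.240 | 13.4% | 267 | 90% |
| ANCOVA, r = 0.7 | 0.714 | 0.283 | 0.198 | 28.6% | 392 | 97.5% |

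**Sensitivity to the reading of the size.** If about 200 means per arm, the unadjusted figure is 2.802 × √(2/200) = 0.280 SD. The percentage reductions in SE are unchanged.

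**Why not a simple change score.** Its multiplier is √(2(1 − r)), which gives a detectable difference of 0.501 SD at r = 0.2, 0.396 at r = 0.5 and 0.307 at r = 0.7. At low correlation that is worse than ignoring the baseline. ANCOVA is never materially worse than either.

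**Time point.** The outcome section sets follow-up at 3 months but synchronises it with the trial's 6-month interview; the analysis section compares the arms at 6 months. As written, the visit to which the mean difference refers is not settled.

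**The case against.** The strongest reply is that the finding rests on silence. A mean difference is an effect measure, and ANCOVA yields one too. The article is condensed, its analysis plan is not shown, and covariate adjustment is often left to that plan. Part of this stands: a reader might infer that the plan specifies a raw comparison, but neither raw nor unadjusted is written. However, the section does fix the estimator, the time point, the within-arm tests and the software, and it gives the comparison no baseline term. If adjustment is intended, the sentence still needs the same clarification.

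A second reply is that nothing is invalid, and this stands in full. Randomisation makes the unadjusted difference unbiased, and its confidence interval already allows for chance baseline imbalance. It would be wrong to infer a biased result.

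A third is that the gain may be slight. This also stands: at r = 0.2 to 0.3 the SE falls by only 2% to 5%, and the article offers no evidence of a higher correlation for these instruments, which include patient-reported cost and experience questionnaires. Nor is there a PROM/PREM power target for lost precision to defeat; the stated objectives concern implementation, usability, acceptability and scaling.

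Finally, a reader might add the planned tests of baseline characteristics to the complaint: "Differences in patient characteristics across study arms will be compared using independent sample t-tests, Wilcoxon-Mann-Whitney tests, and/or Chi-square tests, as appropriate". The article does not say that these tests decide any adjustment, so they change no effect estimate and are not part of this point.

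**Conclusion.** The point holds as a worthwhile improvement to a stated analysis, not as an error. On its natural reading the between-arm comparison leaves the baseline scores unused. With about 100 per arm, adjustment would lower the detectable difference from 0.396 SD to between 0.388 SD (r = 0.2) and 0.283 SD (r = 0.7). This rests on the total-size reading of about 200, complete follow-up, a linear relation with equal SDs in the two arms, and assumed correlations.

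Two limits of scope apply. Baseline scores are planned for the roughly 200 sub-study participants; a reader might take them to cover every patient in the trial, but the article does not say so for the expected 500. The Mobile App Rating Scale is described only at follow-up, so it has no stated baseline to adjust for.

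**What to change.** In Data analysis, Quantitative data, state that for each PROM or PREM measured at baseline the between-arm mean difference is estimated by ANCOVA, with arm, the patient's own baseline score and hospital as terms, and reported with a 95% confidence interval. Exclude the Mobile App Rating Scale from the baseline adjustment.

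A longitudinal model of baseline and follow-up with a common baseline mean is an alternative. With complete data it gives a similar estimate. With missing data the two differ, because the longitudinal model also keeps patients with only one assessment, which sits well with the stated intention-to-treat principle.

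Reconcile the 3-month and 6-month statements so that the adjusted comparison refers to one defined visit.

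The cost is wording only: no new data and no added burden on patients. The Study status section reports one participant recruited when the article was written, so at that stage the change would be fully prospective.

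### The rank test named for within-group change, Wilcoxon-Mann-Whitney, is a test for independent samples, but the baseline and follow-up scores are paired

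*Protocol article*

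**What the plan says.** The protocol article, under Quantitative component - outcome measures, sets up repeated surveys of enrolled patients: "These standardized PROMs/PREMs will be collected at baseline and 3 months for about 200 participants in both study arms". Under Data analysis, Quantitative data, it gives three separate instructions:

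- Patient characteristics between arms: "Differences in patient characteristics across study arms will be compared using independent sample t-tests, Wilcoxon-Mann-Whitney tests, and/or Chi-square tests, as appropriate".
- Survey measures between arms: "The mean difference will be used to compare PROMs and PREMs between the intervention and control arms at 6 months".
- Survey measures within an arm: "Within-group outcomes will be analyzed using paired t-tests and Wilcoxon-Mann-Whitney tests".

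The article names no signed-rank or other paired rank test. It states no significance level for the survey analyses. The only level given is in the sample size paragraph for the randomized trial, under Intervention description: "All sample size equations were calculated using a 5% two-sided level of significance, 80% power and assuming a 1 year follow up".

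**The concern.** Comparing baseline with follow-up in one arm compares two scores from the same patient. The article treats the data that way when it chooses a paired t-test. The rank test beside it belongs to a different design: it pools the two sets of scores, ranks them as if they came from different people, and uses a variance that assumes independence. The two tests in one sentence therefore make incompatible assumptions about the same data.

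Loose wording does not explain this. Two sentences earlier the same full test name stands beside the independent-sample t-test for comparing arms, where it is right. An analyst who followed the text would run the wrong procedure.

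What is at stake is missed within-patient change. Survey ratings are often ordinal or skewed, so the rank test may be the one relied on. Under Qualitative data, the article says the quantitative results will be triangulated with the interviews, so a spurious finding of no change could enter that synthesis. The paired t-test and the rank test could also disagree only because one of them discards the pairing.

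**Working it through.** The article gives no sample size, power or p-value for the within-group analysis, so there is no stated figure to reproduce. The check asks how the named test behaves on paired data.

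**Inputs from the article**
- Paired design and about 200 participants: Quantitative component - outcome measures. Read as a total, this is 200 / 2 = 100 pairs per arm. The wording could also mean 200 per arm.
- Two-sided 5%: stated for the trial's sample size and assumed here for the survey tests.

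**Inputs assumed, because the article gives none**
- Within-patient correlation ρ of 0.3, 0.5 and 0.7, with 0 and -0.3 for contrast.
- Bivariate normal scores.
- A change of 0.3 SD, and 0.2 SD as a second case.

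**Type I error, large-sample formula.** For paired normal scores, the variance of the Wilcoxon-Mann-Whitney statistic is (1 - ρs) times the variance the test assumes, where ρs = (6/π)·arcsin(ρ/2). The true level is

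α = 2·[1 - Φ(1.96 / √(1 - ρs))].

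- ρ = 0.3: ρs = 0.288, √(1 - ρs) = 0.844, 1.96 / 0.844 = 2.32, α = 0.020
- ρ = 0.5: ρs = 0.483, √(1 - ρs) = 0.719, 1.96 / 0.719 = 2.72, α = 0.0064
- ρ = 0.7: ρs = 0.683, √(1 - ρs) = 0.563, 1.96 / 0.563 = 3.48, α = 0.0005
- ρ = 0: α = 0.050
- ρ = -0.3: α = 0.084

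The number of pairs does not enter this formula, so reading the sample as 200 per arm would not change these levels.

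**Simulation.** 100 pairs, 4,000 data sets per setting. Where two values are shown, they come from two separate runs.

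| ρ | Mann-Whitney, type I error | Signed-rank, type I error | Mann-Whitney, power at 0.3 SD | Signed-rank, power at 0.3 SD |
|---|---|---|---|---|
| 0.3 | 0.020 / 0.027 | 0.053 / 0.052 | 0.544 / 0.548 | 0.686 / 0.693 |
| 0.5 | 0.008 / 0.006 | 0.049 / 0.042 | 0.562 / 0.554 | 0.831 / 0.828 |
| 0.7 | 0.001 / 0.001 | 0.052 / 0.050 | 0.575 / 0.586 | 0.964 / 0.962 |

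Over ρ from -0.3 to 0.8 the signed-rank level stays between 0.042 and 0.053. The paired t-test also holds its level (0.046 to 0.053), with power at 0.3 SD of 0.710, 0.851 and 0.971 at ρ = 0.3, 0.5 and 0.7.

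**Hand check of power at ρ = 0.5.** The efficiency factor of both rank tests for normal scores is √(3/π) = 0.977.
- Signed-rank: 0.3·√100 / √(2·(1 - 0.5)) = 3.00; 3.00·0.977 = 2.93; Φ(2.93 - 1.96) = Φ(0.97) = 0.83.
- Mann-Whitney: 0.3·√(100/2)·0.977 = 2.07; (2.07 - 1.96) / 0.719 = 0.16; Φ(0.16) = 0.56.

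Both agree with the simulation. The Mann-Whitney power hardly moves with ρ only because 2.07 happens to lie close to 1.96 in this setting. At a 0.2 SD change it falls as ρ rises, to 0.25, 0.22 and 0.16 at ρ = 0.3, 0.5 and 0.7, while the signed-rank power rises to 0.38, 0.49 and 0.71.

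**The case against.** The best defence concerns consequence, because the wrong test name is plain on the page. The error touches one of two named tests in a within-arm analysis of survey measures, and the valid paired t-test is in the same sentence. The between-arm comparison is a separate instruction and uses a mean difference. The objectives of the realist component (implementation, usability and acceptability, scaling) do not depend on a within-arm rank-test p-value. With positive correlation the test rejects too seldom, so it creates no false claim of benefit. All of this stands, and it limits the severity.

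The defence can also say that the figures are illustrative. Correlation, effect size and normality are assumed. Normal scores are the case in which the paired t-test would serve anyway, and skewed or tied survey scores were not simulated. At ρ = 0.3 the loss is moderate and the two tests would often agree. This stands as a caution on the size. It does not rescue the test, whose p-values are right only if a patient's two scores are uncorrelated, which is implausible for repeated questionnaires.

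A reader might also infer that the authors will judge the application by comparing significance in one arm with its absence in the other. The article does not say so. It specifies a direct between-arm mean difference for the survey measures, so that criticism has no basis in the text.

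**Conclusion.** The point holds as a minor correction. The rank test named for within-group outcomes does not fit paired data. If it is applied as written with positively correlated scores, its p-values are too large and power is lost.

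Under normal scores, 100 pairs per arm and a two-sided 5% level, the true level is about 2-3%, 0.6-0.8% and 0.1% at correlations of 0.3, 0.5 and 0.7. Power for a 0.3 SD change is about 55%, 55% and 58%, against 69%, 83% and 96% for the signed-rank test. The direction needs only a positive correlation. The exact sizes depend on the assumptions, and the power figures depend also on reading the sample as about 100 per arm.

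It would go too far to call all the within-group p-values wrong or the trial's conclusions unsafe. The paired t-test, the between-arm mean difference and the clinical outcomes of the randomized trial are untouched, and false positives are not inflated unless the correlation is negative. The article gives 3 months in one section and 6 months in another for the survey follow-up. That is a separate matter and does not alter this conclusion, since the data are paired at either time.

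**What to change.** Under Data analysis, Quantitative data, and in any statistical analysis plan that carries the sentence over, replace the within-group sentence with: *Within-group change from baseline will be tested with the paired t-test or the Wilcoxon signed-rank test.* Keep Wilcoxon-Mann-Whitney where it is already right, in the comparison of patient characteristics between arms.

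The cost is one term in one sentence. The signed-rank test is a standard procedure in the SAS version the article names. Data collection, sample size and the other analyses do not change. Study status reports one participant recruited, so the correction can be made well before any analysis.
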